### Recruitment and data collection

2.3

Inclusion and exclusion criteria are presented in Table 2. Potential study subjects are recruited (from different hospitals or outpatient clinics) after they are scheduled to undergo ICA at Amsterdam UMC on a clinical basis. A registration log containing anonymized records of all screened patients, who are not enrolled due to either ineligibility or their refusal to participate, will be maintained. After enrollment, information on baseline characteristics and cardiovascular risk factors, including angina-related symptoms, function, and quality of life (assessed according to the Seattle Angina Questionnaire-7 [SAQ-7]), history of present and past diseases, family history of cardiovascular and other diseases, cardiovascular risk factors, current pharmacotherapy, available results of laboratory blood tests, and other diagnostic tests will be collected.

**Table 2 tbl0010:** ADVOCATE-CMR inclusion and exclusion criteria.

Inclusion criteria	- Suspected obstructive CAD - No documented prior history of CAD - Clinical referral for ICA according to the referring clinician’s decision - Competent adult (age ≥18 years) - Signed informed consent
Exclusion criteria	- Acute coronary syndrome - History of coronary revascularization (percutaneous coronary intervention or coronary artery bypass grafting surgery) - History of CAD or acute coronary syndrome (myocardial infarction, unstable angina) - Use of sildenafil or dipyridamole that cannot be terminated - Pregnancy or lactation - Allergic reaction to iodized contrast - Concurrent or prior (within last 30 days) participation in other research studies using interventional drugs - Extensive comorbidities (i.e., cancer, other severe chronic diseases) - Contraindication for CMR with GBCA (including severe claustrophobia, MR unsafe implants/devices or MR conditional devices not suitable for 3T scanner, acute or severe renal failure with eGFR <30 mL/min/1.73 m2, known hypersensitivity for GBCA) - Contraindications for adenosine usage (including hypersensitivity to adenosine/dipyridamole/regadenoson, second- or third-degree atrio-ventricular block, sick sinus syndrome, sinus bradycardia [heart rate <40 bpm], long QT syndrome, severe hypertension [> 220/120 mmHg], systolic blood pressure <90 mmHg, concomitant use of dipyridamole, severe asthma, or severe chronic obstructive pulmonary disease)

*CAD* coronary artery disease, *CMR* cardiac magnetic resonance, *eGFR* estimated glomerular filtration rate, *GBCA* gadolinium-based contrast agent, *ICA* invasive coronary artery, *MR* magnetic resonance

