## Abstract

**Background:**

First-pass stress-perfusion cardiovascular magnetic resonance (CMR) imaging is the guidelines-recommended non-invasive test for the detection of obstructive coronary artery disease (CAD). Recently developed quantitative perfusion CMR (QP CMR) allows quantification of myocardial blood flow. Moreover, the latest developments established several methods of CAD assessment without the need for a contrast agent, including stress T1 mapping reactivity (∆T1) and oxygenation-sensitive CMR (OS-CMR). These methods might eliminate the need for contrast administration in clinical practice, reducing time, invasiveness, and costs, thereby simplifying the evaluation of patients with suspected obstructive CAD. The ADVOCATE-CMR study aims to validate QP CMR, ∆T1, and OS-CMR imaging against invasive fractional flow reserve (FFR) for the detection of obstructive CAD. The study also aims to head-to-head compare the diagnostic accuracy of these CMR techniques with the conventional visual assessment of stress-perfusion CMR and to correlate them to short- and long-term clinical outcomes.

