However, it must be noted that GBCA-based QP CMR, despite its advantages over the conventional visual assessment approach, is associated with some clinically relevant drawbacks. First-pass perfusion CMR imaging (either conventional or QP) requires administration of GBCA, which for this purpose in most countries is used off-label. In addition, GBCAs are advised not to be used in patients with severe renal dysfunction and have been associated with the rare development of nephrogenic systemic fibrosis. Furthermore, its repeated administration may cause accumulation of gadolinium in brain tissues, albeit of unknown clinical significance [39]. Therefore, there are still some regulations and safety concerns regarding the use of GBCA [40]. Due to these matters, the development and clinical validation of alternative, accurate methods for CMR ischemia detection without the need for GBCA are warranted. Recently, novel, non-GBCA-based CMR imaging strategies have been proposed for evaluation of myocardial ischemia, including stress T1 mapping reactivity (∆T1) and oxygenation-sensitive CMR (OS-CMR). These methods, however, have not been introduced into diagnostics and clinical decision-making in patients with CAD due to the lack of proper validation against the invasive gold standard measures in a real-world population.

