### Study design

2.1

ADVOCATE-CMR is a single-center, observational, prospective, cross-sectional cohort study performed at the Amsterdam University Medical Centers—Location VUmc. The study is performed in accordance with the principles of the Declaration of Helsinki, and all patients need to provide informed written consent to participate. The study protocol has been approved by the local ethics committee (Medisch Ethische Toetsingscommissie Amsterdam UMC) and is registered in ClinicalTrials.gov under the number NCT06419894.

The flowchart of the study is presented in Fig. 3. The study will enroll 182 symptomatic patients with suspected obstructive CAD scheduled for ICA according to the decision of the treating clinician (see Section 2.9). Before ICA, all study participants will undergo CMR imaging, including rest and adenosine stress perfusion, rest and adenosine stress T1 mapping, and OS-CMR with breathing maneuvers. Subsequently, within 6 weeks, ICA will be performed including FFR, instantaneous wave-free ratio (iFR), resting ratio between proximal and distal coronary pressures over the entire resting cycle period (Pd/Pa), coronary flow reserve (CFR), and index of microvascular resistance (IMR) measurements in all main coronary arteries. A second follow-up CMR scan according to the same scan protocol as the first CMR scan will be performed at 3 months after ICA (or 3 months after revascularization, if performed separately more than 1 day following ICA). Clinical follow-up will be at 3, 6 months, 1 and 3 years after the ICA (or revascularization if applicable).

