- Diagnostic accuracy (sensitivity, specificity, accuracy, AUC, PPV, NPV) of ΔT1 to detect obstructive CAD, as defined by FFR - Diagnostic accuracy (sensitivity, specificity, accuracy, AUC, PPV, NPV) of OS-CMR (B-MORE) to detect obstructive CAD, as defined by FFR - Head-to-head comparison of diagnostic accuracies (sensitivity, specificity, accuracy, AUC, PPV, NPV) of QP CMR (stress MBF, stress rMBF, MPR, rMPR), ΔT1, OS-CMR, and conventional visual assessment of GBCA-based first-pass perfusion imaging to detect obstructive CAD, as defined by FFR - Diagnostic accuracy (sensitivity, specificity, accuracy, AUC, PPV, NPV) of QP CMR (stress MBF, stress rMBF, MPR, and rMPR) to detect obstructive CAD, as defined by iFR and resting Pd/Pa - Diagnostic accuracy (sensitivity, specificity, accuracy, AUC, PPV, NPV) of ΔT1 to detect obstructive CAD, as defined by iFR and resting Pd/Pa - Diagnostic accuracy (sensitivity, specificity, accuracy, AUC, PPV, NPV) of OS-CMR (B-MORE) to detect obstructive CAD, as defined by iFR and resting Pd/Pa - Head-to-head comparison of diagnostic accuracies (sensitivity, specificity, accuracy, AUC, PPV, NPV) of QP CMR (stress MBF, stress rMBF, MPR, rMPR), ΔT1, OS-CMR, and conventional visual assessment of GBCA-based first-pass perfusion imaging to detect obstructive CAD, as defined by iFR and resting Pd/Pa - Relation of stress and rest MBF and rMBF, MPR and rMPR, ΔT1 and OS-CMR markers to SAQ-7 Summary score, SAQ-7 Angina Frequency score, SAQ-7 Physical Limitation score, SAQ-7 Quality of Life score (before and after revascularization), and Rose Dyspnea Scale score - Prognostic value of QP CMR (stress MBF, stress rMBF, MPR, and rMPR), stress T1 mapping reactivity and OS-CMR in predicting occurrence of a 1) composite of cardiovascular death, myocardial infarction, ischemia-driven coronary revascularization or stroke; 2) composite of myocardial infarction or ischemia-driven coronary revascularization; 3) composite of cardiovascular death, stroke or myocardial infarction; 4) myocardial infarction; 5) ischemia-driven coronary revascularization; 6) stroke; 7) death from any cause; 8) cardiovascular death
*Tertiary endpoints*

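### Referral to ICA may rest on an earlier perfusion scan, which can lower perfusion specificity relative to ΔT1 and OS-CMR in the pooled comparison; add a supporting analysis by referral route

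*Protocol article*

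**What the plan says.** Entry follows the clinical decision. Section 2.1 describes patients "scheduled for ICA according to the decision of the treating clinician", and Table 2 lists "Clinical referral for ICA according to the referring clinician" among the inclusion criteria. Section 2.3 says: "Potential study subjects are recruited (from different hospitals or outpatient clinics) after they are scheduled to undergo ICA at Amsterdam UMC on a clinical basis". No criterion requires or excludes a prior non-invasive test.

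The article treats the test families differently with regard to clinical use. Its abstract says that stress-perfusion CMR "is the guidelines-recommended non-invasive test for the detection of obstructive coronary artery disease (CAD"). Of ΔT1 and OS-CMR, the Background says: "These methods, however, have not been introduced into diagnostics and clinical decision-making in patients with CAD".

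Table 1 lists the comparison of QP CMR, ΔT1, OS-CMR and visual perfusion as a secondary endpoint, in an entry that begins: "Head-to-head comparison of diagnostic accuracies (sensitivity, specificity, accuracy, AUC, PPV, NPV) of QP CMR (stress MBF, stress rMBF, MPR, rMPR), ΔT1, OS-CMR, and conventional". Section 2.9.2 computes performance measures for the entire cohort, compares AUCs by DeLong and compares sensitivity, specificity and accuracy by McNemar's test. It mentions no split by referral route. Section 2.3 already collects available results of other diagnostic tests.

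**The concern.** An FFR-negative patient who reached ICA because of a positive perfusion scan was a perfusion false positive before enrolment, and is more likely than average to be one again on the study scan. FFR-negative patients whose earlier scan was negative tend not to reach ICA. The FFR-negative group can therefore hold too many perfusion false positives. ΔT1 and OS-CMR can be affected only through correlation with the earlier scan, because neither is used to refer patients.

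Blinded reading (section 2.4.6) and FFR in all main arteries (section 2.5) protect against reading bias and differential verification within the cohort. They do not change who enters it.

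At stake is a McNemar result on specificity that favours a contrast-free test partly through selection. Specificity matters for the gatekeeper role that the article hopes CMR will fill. The specificity of QP CMR in the primary endpoint may fall as well.

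**Working it through.** **1. The plan's own figure.** Section 2.9.1 states 80% power for AUC 0.90 against 0.81 with 74 positive and 90 negative patients, two-sided 0.05. With Hanley-McNeil variances under both hypotheses, power is 79.9%, so the figure reproduces. Selection is a separate matter from this calculation.

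**2. Specificity among patients referred on a positive scan.** The documents give no share, specificity or correlation with a prior scan, so all three are assumed. Within FFR-negative patients, take bivariate normal scores for the prior perfusion scan and a study test, each with unselected specificity 0.85 (threshold t = 1.036), and correlation ρ between them. Then

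P(study negative | prior positive) = [0.85 − Φ₂(t, t; ρ)] / 0.15

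This is 0.770, 0.672, 0.552 and 0.391 for ρ = 0.2, 0.4, 0.6 and 0.8.

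**3. Overall specificity and the gap.** Let f be the share of enrolled FFR-negative patients who were referred on a positive perfusion scan. Overall specificity is 0.85(1 − f) + f × the value above. With ρ = 0.6 for study perfusion and 0.4 or 0.2 for a contrast-free test:

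| f | Perfusion (0.6) | Contrast-free (0.4) | Contrast-free (0.2) | Gap, points |
|---|---|---|---|---|
| 10% | 0.820 | 0.832 | 0.842 | 1.2-2.2 |
| 30% | 0.761 | 0.797 | 0.826 | 3.6-6.5 |
| 50% | 0.701 | 0.761 | 0.810 | 6.0-10.9 |

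The gap is f × (0.672 − 0.552) to f × (0.770 − 0.552). It is zero when both tests have ρ = 0.6. The absolute fall in perfusion specificity alone, over ρ = 0.4 to 0.8, is to 0.83-0.80, 0.80-0.71 and 0.76-0.62. That range is not the between-test effect.

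**4. How many candidates this implies.** Suppose perfusion-route candidates enter only if positive and all others enter unselected. The share s of FFR-negative candidates taking the perfusion route is then f / [f + 0.15(1 − f)]: 43% for f = 10%, 74% for 30% and 87% for 50%.

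**5. Sensitivity and AUC.** These come from a simulation of 1.5 million patients per scenario. Assumptions: true AUC 0.85 for all tests, 30% prevalence before referral, ρ = 0.6 for perfusion, and ρ = 0.4 to 0.2 for the contrast-free test. Differences are perfusion minus contrast-free. The share is of candidates before selection.

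| Candidate share | Specificity, points | Sensitivity, points | AUC |
|---|---|---|---|
| 50% | −2.2 to −3.9 | +1.5 to +2.8 | −0.002 to −0.004 |
| 75% | −4.5 to −8.4 | +2.4 to +4.3 | −0.007 to −0.015 |
| 100% | −11.2 to −20.5 | +3.4 to +6.0 | −0.025 to −0.054 |

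If the contrast-free test is uncorrelated with the prior scan, the AUC difference is −0.007, −0.024 and −0.082. If it is correlated 0.6, as perfusion is, the AUC difference is at most 0.001 in size.

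**6. Effect on the planned McNemar test.** Take 90 FFR-negative patients, two tests of equal true specificity 0.85, and correlation 0.6 between the study tests (the between-test value in section 2.9.1). The chance of a significant specificity result wrongly favouring the contrast-free test is about 1.4% with no selection. Under the correlations in step 3 it is 2-5% at f = 10%, 7-20% at 30% and 16-49% at 50%.

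**7. Primary endpoint.** With QP AUC 0.90, prior-scan AUC 0.81 and ρ = 0.6, QP specificity falls from 0.818 to 0.768 at 50% candidate share and 0.581 at 100%. AUC becomes about 0.897 and 0.86, and power against 0.81 falls from 80% to about 76% and 27%.

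**The case against.** Nothing in the article is misstated, and recruiting patients already due for ICA is what makes invasive reference measurements in every main artery possible. No passage says that anyone was referred on perfusion imaging. The hope that CMR may become a gatekeeper for ICA suggests that it does not yet control access, so the share could be low. As step 4 shows, f = 30% or 50% needs most candidates to arrive by perfusion. A full protocol or SAP might also contain an analysis by referral route. This stands: the exposure is possible and its size unknown.

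The correlation argument also stands. ΔT1 uses the same adenosine stress as perfusion, and microvascular dysfunction is a plausible shared source of false positives in FFR-negative patients. A reader might infer that the specificity of ΔT1 and B-MORE is untouched. The documents do not support that: any correlation with the earlier scan lowers theirs too, and equal correlation removes the tilt. The argument is stronger for OS-CMR, which uses breathing maneuvers and a different signal.

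A reader might also infer a general advantage for the contrast-free tests. Sensitivity moves toward perfusion, and AUC, the metric behind the sample size, barely moves at moderate shares. QP against visual perfusion is largely outside the issue, since both are perfusion tests.

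What the objection does not remove is that the entry rule lets one comparator family influence enrolment, and that the described specificity comparison pools all referral routes.

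**Conclusion.** The concern holds in a limited form. The pooled comparison may understate perfusion specificity relative to OS-CMR, and less probably relative to ΔT1, while somewhat overstating perfusion sensitivity. Under the assumed correlations the specificity gap is about 1-2, 4-7 and 6-11 points at 10%, 30% and 50% of enrolled FFR-negative patients. It vanishes if the correlations are equal. AUC is materially affected only if most candidates come by perfusion imaging.

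Two further readings go too far. The head-to-head is a secondary endpoint and not the study's primary claim, which is QP CMR against FFR. The selection does not invalidate the primary endpoint either: QP specificity may fall, but its AUC changes little unless perfusion referral is very common. This is an inexpensive improvement to a defensible design, not an error in it.

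**What to change.** 1. Keep the all-patient analysis as the main one.
2. Record for each patient the test that prompted referral for ICA. Recruitment is ongoing, and other diagnostic test results are already collected.
3. Prespecify a supporting head-to-head of sensitivity, specificity and AUC, stratified by referral route, with a version that excludes patients referred on stress-perfusion imaging. Report the share on each route.
4. Do not claim better specificity of ΔT1 or OS-CMR over perfusion on the pooled result alone if the supporting analysis does not agree in direction.

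The cost is one eCRF field and one additional analysis. Intervals in the restricted set will be wider, and that set is itself selected by other tests. This is why it should not replace the main analysis. Scaling the 80%-power noncentrality (1.96 + 0.84 = 2.80) by √0.7 or √0.5 leaves about 65% power if 30% of patients are dropped, or 51% if half are.

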### CMR imaging

2.4

All subjects included in the study will undergo adenosine stress CMR using a 3T whole-body magnetic resonance imaging (MRI) scanner (Magnetom Vida, Siemens Healthcare, Erlangen, Germany) after abstaining from caffeine and xanthine for 24 h. The CMR protocol is presented in Fig. 4 and typical sequence parameters are listed in Table 3. After the CMR examination, patients will be asked about symptoms experienced during breathing maneuvers and adenosine administration. They will also be asked about their preference for the stress testing method (adenosine or breathing maneuvers) during the CMR examination.

**Fig. 4 fig0020:**
[figure not shown]
ADVOCATE-CMR imaging protocol. *2CH* two-chamber view, *3CH* three-chamber view, *4CH* four-chamber view, *AIF* arterial input function, *bSSFP* balanced steady-state free precession, *GBCA* gadolinium-based contrast agent, *i.v.* intravenously, *LAX* long axis, *LGE* late gadolinium enhancement, *mSSFP* modified steady-state free precession, *OS* oxygenation-sensitive, *SAX* short axis

**Table 3 tbl0015:** Typical sequence parameters used in the scanning protocol of ADVOCATE-CMR study.

Type of CMR imaging	Planes	Sequence	Typical parameters
Cine	• LAX ○ 2CH ○ 3CH ○ 4CH • SAX stack	bSSFP	• In-plane resolution 1.5 × 1.5 mm^2^ • Slice thickness 5 mm • TE 1.6 ms • TR 3.7 ms • Matrix size 240 × 240* • FoV 320-400 mm* • FA 80° • GRAPPA/T-pat factor 2
Oxygenation-sensitive sequence	• SAX ○ Basal ○ Mid-ventricular	bSSFP	• In-plane resolution 1.9 × 2.3 mm^2^ • Slice thickness 10 mm • TE 1.73 ms • TR 3.45 ms • Matrix size 192 × 120* • FoV 320-400 mm* • FA 35° • GRAPPA/T-pat factor 2
T1 mapping	• SAX ○ Basal ○ Mid-ventricular ○ Apical	MOLLI 5(3)3	• In-plane resolution 1.4 × 2.1 mm^2^ • Slice thickness 8 mm • TE 1.06 ms • TR 2.54 ms • TI: Start T1 100 ms, increment 80 ms • Matrix size 256 × 169* • FoV 320-400 mm* • FA 35° • GRAPPA/T-pat factor 2
Quantitative perfusion	• SAX ○ Basal ○ Mid-ventricular ○ Apical	Saturation recovery turbo spoiled gradient echo	• In-plane resolution 2.3 × 2.3 mm^2^ • Slice thickness 8 mm • TE 1.18 ms • TR 2.64 ms • TS 100 ms • Matrix size 160 × 160 • FA 12° • GRAPPA/T-pat factor 2
Late gadolinium enhancement	• LAX ○ 2CH ○ 3CH ○ 4CH • SAX stack	2D segmented inversion recovery gradient echo	• In-plane resolution 1.8 × 2.4 mm^2^ • Slice thickness 8 mm • TE 1.2 ms • TR 3.1 ms • TI adjusted to null the myocardium (based on the modified look-locker approach) • Matrix size 192 × 144* • FoV 320-400 mm* • FA 10°

*2CH* two-chamber view, *2D* two-dimensional, *3CH* three-chamber view, *4CH* four-chamber view, *bSSFP* balanced steady-state free precession, *FA* flip angle, *FoV* field of view, *GRAPPA* generalized autocalibrating partially parallel acquisition, *LAX* long axis, *MOLLI* modified look-locker inversion recovery, *mSSFP* modified oxygenation-sensitive balanced steady-state free precession, *SAX* short axis, *TE* time of echo, *TI* time of inversion, *TR* time of repetition, *TS* time of saturation

* Depending on the patient’s size, increase phase FoV

#### Pre-scan procedure (outside the scanner)

2.4.1

Every participant scheduled for a CMR scan will be checked to pass the routine MRI safety screening of Amsterdam UMC, which includes questions on past medical and surgical history and the presence of any implant, device, or metallic foreign body inside or at the body surface of the participant. Any patient who does not meet the safety requirements will be excluded from the study. Eligible study candidates will be instructed and practice the breathing maneuver, including 60 s of paced hyperventilation followed by a maximal voluntary breath-hold (for as long as possible, preferably 60 s). An instructional video is used to facilitate the instructions for patients.

#### CMR acquisition of cine images

2.4.2

At the beginning of the CMR examination, localizer images will be obtained to define long-axis (LAX) and short-axis (SAX) planes. Cine images (LAX two-, three-, and four-chamber views and SAX) will be acquired with a balanced steady-state free precession (bSSFP) pulse sequence during breath-hold at end-expiration. Subsets of SAX images at the basal, mid-ventricular, and apical levels will be selected and used to ensure consistent slice positioning across all sequences used. SAX imaging planes will be determined using the end-systolic phase of LAX four-chamber cine images. Care will be taken to avoid inclusion of the left ventricular outflow tract in the basal slice.

#### Acquisition of OS-CMR images

2.4.3

Baseline OS acquisition will be acquired using a modified OS bSSFP (mSSFP; [65]). This acquisition will take ∼10 s and will be performed in two SAX slices (basal and mid-ventricular) at end-expiration. The obtained images will be checked for slice location and the absence of significant artifacts. If necessary, baseline OS sequences will be repeated to achieve adequate image quality.

The following continuous acquisition will be performed using the same slice locations and sequence parameters. It will take 2 min, including 1 min of hyperventilation at a frequency of 30 breaths/min and 1 min of breath-hold at comfortable end-expiration. Patients will be guided through the breathing maneuvers by pre-recorded instructions played through the MRI audio system. After breathing maneuvers, patients will be allowed to breathe normally for 2–3 min without any image acquisition.

#### CMR acquisition of T1 mapping

2.4.4

Native T1 mapping will be obtained at three image SAX planes (basal, mid-ventricular, and apical) using a modified look-locker inversion recovery (MOLLI) 5(3)3 sequence at rest (baseline) and after at least 3 min of constant intravenous infusion of adenosine at a dose of 140 μg/kg/min. To evaluate adenosine effectivity, heart rate increase and drop in blood pressure will be analyzed. With suspicion of insufficient effect of adenosine (heart rate increase less than 10 beats per minute), the dose will be increased first to 180 μg/kg/min for 2–3 min and, if ineffective, to 210 μg/kg/min for 2–3 min [66]. At the beginning of image acquisition, patients will be asked to hold their breath as long as possible and breathe slowly thereafter.

